### Randomization

Randomization will be controlled by an independent clinical research coordinator (CRC). First, the randomization form with the basic information of the participant who passed the screening phase will be transmitted by facsimile to the independent statistician. The randomization number in the randomization form will be left blank before arrival at the statistician. The statistician will then decide the randomization number based on the allocation sequence, which will be generated by a random number creation program in advance. The statistician will then return the randomization form filled in with the established number (specific ID number) to the CRC. The ratio of randomization allocation to the sites should be 1:1. The CRC will then inform the investigators of the specific ID number. The completion of this procedure will be guaranteed by the research organization.

### Blinding

In this trial, investigators will not be in contact with the CRC, the clinical pharmacist, or the statistician. The CRC will be separated from all researchers, thus the researchers will not have any influence on enrollment or randomization. The statistician will receive the randomization form by facsimile, fill in the blank and return the form; thus, any contact with other researchers will not occur.

### Setting

In this stage, 2 or more centers will be added to the list of centers participating in the stage-one trial.

### Interventions

1. Tripterygium Wilfordii Polyglycoside and its associated placebo. To completely blind the patients, the Tripterygium Wilfordii Polyglycoside tablet and placebo are packaged identically. Either Tripterygium Wilfordii Polyglycoside or the placebo will be prescribed at 10 mg 3 times a day immediately after meals.

2. Yi Shen Juan Bi (YSJB) and its associated placebo. YSJB and its placebo are made by Qingjiang Pharmaceutical Co., Ltd (Z10890004). The placebo, which has an identical appearance, is made from cane sugar and will be prescribed at the same dosage as the YSJB, which will be 1 pocket (8 g) 3 times a day immediately after meals.

3. Methotrexate (MTX) and its associated placebo. Methotrexate tablets and the placebo will be provided by Shanghai Xinyi Pharmaceutical Co., Ltd (Drug registration Number: Z070404). MTX and its placebo are available in 2.5-mg tablets and will be administered orally at an initial dose of 5 mg/week (up to 15 mg/week, 2.5 mg/per time). For the remission period, the standard dose will range from 1 tablet/week (2.5 mg) to 3 tablets/week (7.5 mg).

4. Sulfasalazine (SSZ) and its associated placebo. Sulfasalazine tablets and the placebo were provided by Xi'an Kangbaier Pharmaceutical Co., Ltd (Drug registration Number: Z070404). SSZ and its placebo are available in 0.25 g tablets and will be taken at an initial dose of 0.25 g twice a day (up to 0.5-1 g, 4 times/day). For the remission period, the standard dose will be 0.5 g (2 tablets) 3-4 times/day.

Participants in the CM therapy will be given Tripterygium Wilfordii Polyglycoside and YSJB along with the MTX and SSZ placebos. Participants in the positive control therapy will be given MTX and SSZ (Western combination therapy) along with the Tripterygium Wilfordii Polyglycoside and YSJB placebos.

### Outcome measures

The primary efficacy endpoint is the ACR20 response. Secondary efficacy endpoints include the ACR50 and ACR70 responses and the individual components of the ACR. CM symptoms, joint function, physical exam, laboratory tests, and HAQ will be tested. Safety endpoints include AEs and laboratory abnormalities. The timeline of the participants' progression through the trial in stage two is shown in Table 2.

**Table 2 T2:** Timeline of participants' progression through the stage-two trial

Assessment	Visit 1	Visit 2	Visit 3	Visit 4	Visit 5	Visit 6	Visit 7	Visit 8	Visit 9
	Screen	Base	2^nd ^w*	4^th ^w	8^th ^w	12^th ^w	16^th ^w	20^th ^w	24^th ^w (or withdrew)
Medical history	●								
Physical examination	●		●	●	●	●	●	●	●
Joint function		●	●	●	●	●	●	●	●
Swollen joint count		●	●	●	●	●	●	●	●
Tender joint count		●	●	●	●	●	●	●	●
Physician global status	●	●	●	●	●	●	●	●	●
Patient global assessment		●	●	●	●	●	●	●	●
Morning stiffness		●	●	●	●	●	●	●	●
Pain at rest		●	●	●	●	●	●	●	●
Pattern based on CM (symptoms)	●	●	●	●	●	●	●	●	●
Blood test		●	●	●		●			●
Routine urine test		●	●	●		●			●
Stool routine test		●				●			●
CRP		●				●			●
ESR		●				●			●
RF		●				●			●
ALT		●	●	●		●			●
AST		●	●	●		●			●
Bilirubin		●				●			●
Cr		●	●	●		●			●
BUN		●	●	●		●			●
VAS		●		●	●	●	●	●	●
HAQ		●				●			●
EGG		●							●
X-ray		●							●
Adverse events		●	●	●	●	●	●	●	●

Notes: *w = week

### Ethical considerations

Approvals from the appropriate research ethics committees will be obtained at ten study centers. All patients will be asked to provide written, informed consent before participating.

### Quality control

The identification, registration and subsequent flow of participants in the trial will be governed by the trial standard operational protocol (SOP) at all sites. The sites' Case Report Form (CRF) completion and compliance with standard operation procedures will be audited. Clinical research associates, at regular periods, will monitor the clinical trial procedures, such as compliance with administration and voluntary withdrawal of participants. In particular, the reasons for withdrawal will be fully documented in the CRF.

### Statistical analysis

Patients will be included for analysis according to the randomized treatment arm regardless of the actual treatment received during the study. All efficacy endpoints will be analyzed using the intent-to-treat analysis set, which will include all randomized patients regardless of whether they received an investigational product. The safety dataset will also include all patients who received ≥ 1 dose of an investigational product. The primary efficacy endpoint will be used to compare the ACR20 response rate at week 24 in the CM group with that of the biomedicine group. All secondary endpoints will be tested sequentially in a pre-specified order to control the one-error rate at 5% (two-sided). The comparisons of proportions (for dichotomous variables) among treatment arms will be performed using Fisher's exact test. For dichotomous variables, missing values will be imputed using a non-responder imputation method; for continuous variables, the primary analysis will be based on observed cases.

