### Design

This is a two-stage, multi-center trial in the management of RA. The first-stage trial is an open-label trial and aims to explore which groups of CM-related symptoms correlates with better efficacy, and the second-stage trial is a 24-week randomized, controlled, double-blind, double-dummy clinical trial that incorporates the group of symptoms identified in the first-round trial in the inclusion criteria.

The hypotheses for the two-stage clinical trial to be tested are as follows:

1. The CM therapy is safe, acceptable and feasible, and at least 80% of the subjects will complete the CM therapy.

2. The specified group of participants treated with CM therapy will demonstrate significantly improved ACR20 responses compared to the positive control group.

A flow chart of the study design is shown in Figure 1.

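### The stage-two grouping rule analyses every patient by randomised arm and makes no exception for safety, so harms in a patient who took the other arm's drugs are counted under the wrong regimen

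*Protocol article*

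**What the plan says.** Three consecutive sentences in the protocol article (Stage two of the Trial, Statistical analysis) matter here.

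- Grouping, with no restriction to a type of endpoint: "Patients will be included for analysis according to the randomized treatment arm regardless of the actual treatment received during the study".
- Efficacy population: "All efficacy endpoints will be analyzed using the intent-to-treat analysis set, which will include all randomized patients regardless of whether they received an investigational product".
- Safety population: "The safety dataset will also include all patients who received ≥ 1 dose of an investigational product".

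The stage-two Outcome measures section defines what is to be tabulated: "Safety endpoints include AEs and laboratory abnormalities". Both arms take active drugs. In the Interventions section, one arm is described as "Participants in the CM therapy will be given Tripterygium Wilfordii Polyglycoside and YSJB along with the MTX and SSZ placebos" and the other as "Participants in the positive control therapy will be given MTX and SSZ (Western combination therapy) along with the Tripterygium Wilfordii Polyglycoside and YSJB placebos". The first hypothesis in the Design section reads "The CM therapy is safe, acceptable and feasible, and at least 80% of the subjects will complete the CM therapy". No other section groups safety data by treatment received.

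**The concern.** Analysis by randomised arm is the right choice for a superiority test on ACR20. It preserves the randomised comparison, and any dilution from cross-exposure works against the claim of superiority. For harms the same dilution works the other way: it hides a difference in toxicity and is anti-conservative.

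The article does more than leave the safety grouping open. It states a rule, says that actual treatment is to be disregarded, and exempts nothing. An analysis plan that grouped harms by treatment received would have to depart from that sentence. Because each arm has its own active drugs, a liver, blood or renal abnormality in a control patient who took the active herbal products would appear in the methotrexate–sulfasalazine column, and the reverse. The safety profile of the CM therapy is part of the first hypothesis, so attribution to the right regimen matters.

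**Working it through.** **Step 1: reading the text.** The first sentence covers patients and analysis in general. The second introduces efficacy endpoints and names their population, so the efficacy restriction begins there and not in the first sentence. The third says who enters the safety dataset and does not say how they are grouped. The only grouping instruction in the section is therefore the first sentence.

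**Step 2: stated figures.** No stated figure depends on the safety grouping. The sample size is checked only for the denominators. With 76% and 53%, two-sided α = 0.05 and 90% power, the pooled-variance formula without continuity correction gives

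n = [1.960·√(2·0.645·0.355) + 1.282·√(0.76·0.24 + 0.53·0.47)]² / 0.23² ≈ 88.9, or 89 after rounding up.

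The article gives 88, and 88/0.80 = 110 per group. Changing the safety grouping leaves these numbers as they are.

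**Step 3: effect of the rule.** Let pA and pB be the true harm rates on the two regimens, and let a fraction m of each arm take the other arm's drugs completely. Tabulated by randomised arm, the expected rates are

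- arm A: (1 − m)·pA + m·pB
- arm B: (1 − m)·pB + m·pA
- difference: (1 − 2m)·(pA − pB)

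Assumed rates, not in the documents: pA = 10%, pB = 2%, true difference 8.0 points.

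| m | Patients per arm of 110 | Arm A shown | Arm B shown | Difference shown (points) |
|---|---|---|---|---|
| 0 | 0 | 10.00% | 2.00% | 8.0 |
| 2% | 2.2 | 9.84% | 2.16% | 7.7 |
| 5% | 5.5 | 9.60% | 2.40% | 7.2 |
| 10% | 11 | 9.20% | 2.80% | 6.4 |

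With commoner harms, an assumed 20% versus 10%, the true 10.0 points become 9.8, 9.6, 9.1 and 8.0 when 1, 2, 5 and 11 patients per arm are switched.

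If switching goes one way only, the factor is (1 − m). At m = 2%, 5% and 10% the 8.0 points become 7.8, 7.6 and 7.2.

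**Step 4: rare events.** Rates are a poor guide when there is one case. If the only serious event falls in a patient who took the other arm's drugs, a true 1 versus 0 is tabulated as 0 versus 1.

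**The case against.** The strongest reply is that the first two sentences together state the intention-to-treat principle and nothing more. The safety set has its own basis, and its grouping is merely unstated, which a condensed article may leave to an analysis plan. The drafting is loose, and the word that links the safety sentence to the rest is thin support for carrying the rule over. This reading is possible and the authors may well have meant it. It is not what the text says: the opening sentence has no efficacy limit, and the limit appears only in the sentence that follows. At the least, the wording needs correcting before an as-treated safety analysis can be consistent with it.

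A reader might also infer several stronger things that the documents do not support.

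- *That misallocation is likely here.* Each patient takes four products, and the randomisation form travels by fax. But the Randomization section describes a sequence generated in advance and an independent statistician, and nothing is said of how kits are dispensed or how often errors occur. The frequency is unknown.
- *That both regimens' harms would be reported too low.* For a harm that both regimens cause at different rates, only the more toxic regimen is understated. The other is overstated, as in the move from 2.00% to 2.16% above.
- *That a planned safety test is biased.* The first hypothesis says "The CM therapy is safe, acceptable and feasible" and adds a completion target. It sets no comparison of harms between arms. What is affected is the descriptive safety table and the attribution of events.
- *That the (1 − 2m) factor covers any mix-up.* It assumes complete, symmetric exchange of regimens. An error in one of the four products gives partial exposure, which the formula does not model.

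**Conclusion.** The concern holds as a defect of wording with a limited consequence. The article states one grouping rule for all analyses and gives the safety dataset no exception, so harms after cross-exposure are counted under the regimen that was not taken. The direction is clear: the arms' harm rates are pulled together, and a rare serious event can be misattributed.

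The size rests wholly on assumed harm rates and an assumed full, symmetric switch. On those assumptions the loss is about 0.3 of 8.0 points at m = 2% and 1.6 points at m = 10%. It is nil with no cross-exposure. Sample size and efficacy results do not change. This is a cheap improvement and does not threaten the trial's main conclusion.

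**What to change.** In the stage-two Statistical analysis section, confine the first sentence to efficacy, for example: *For efficacy endpoints, each patient is assigned to the arm allocated at randomisation, whatever was taken.* Then complete the safety sentence: *AEs and laboratory abnormalities are summarised in all patients with at least one dose, grouped by the active regimen actually received; patients exposed to active drugs of both regimens are listed separately.*

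The text change is two sentences. It does have a small cost in data. In a double-blind, double-dummy trial the active product taken can be established only after unblinding, by reconciling dispensing records with the allocation. The Quality control section provides for monitoring of compliance with administration but does not say that the product actually received is recorded, so the sponsor should confirm that those records are kept.

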### Sample size

This trial at stage 2 is designed as an active control superiority trial and intended to show superiority of CM intervention. The sample size calculation is based on the ACR20 response rate of the stage one of the trial. The primary results of the stage one trial (76% ACR20 response of CM intervention in the patients with the efficacy positively related CM symptoms) and our previous clinical data (53% ACR20 response in Western medicine intervention in the patients with the efficacy positively related CM symptoms). The sample size was established by comparing the rates of effectiveness between CM and Western medicine interventions (set α = 0.05, *β*= 0.10). Sample size could be 88 in both groups. With a dropout rate for follow-up as 20%, the sample size for each group could be 110 and 220 in the two groups.

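### The primary ACR20 comparison is fixed as an unadjusted Fisher's exact test although every ACR component is measured at baseline: valid, but it gives up precision at no saving

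*Protocol article*

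**What the plan says.** All references are to stage two of the Protocol article.

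- **Endpoint and test.** Statistical analysis makes ACR20 at week 24 the primary contrast between the CM and control arms: "The primary efficacy endpoint will be used to compare the ACR20 response rate at week 24 in the CM group with that of the biomedicine". The same section gives one method for every binary outcome: "The comparisons of proportions (for dichotomous variables) among treatment arms will be performed using Fisher's exact test". It names no covariate, centre term or stratified method. Missing binary outcomes are counted as non-response, and all randomised patients are analysed.
- **Baseline data.** Table 2 (Outcome measures) marks "Swollen joint count" at Visit 2 (Base). It also marks tender joint count, patient and physician global assessments, pain at rest, VAS, HAQ, CRP and ESR at that visit.
- **Centres.** Ethical considerations says "Approvals from the appropriate research ethics committees will be obtained at ten study centers". Randomization says "The ratio of randomization allocation to the sites should be 1:1" but names no stratification factor.
- **Sample size.** The calculation uses "set α = 0.05, *β*= 0.10", a CM rate given as "76% ACR20 response of CM intervention in the patients with the efficacy positively related CM symptoms", and 53% for the control. It arrives at 88, then 110 per group (220 in all) after 20% dropout.

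**The concern.** The trial claims superiority on one binary endpoint and aims for 90% power. If baseline disease activity predicts response, a pooled 2x2 comparison leaves that explainable variation in the error term and does not correct for chance imbalance between the arms. The measurements needed to do better are already scheduled. Fisher's test is also conservative at this size, so some power is lost even before covariates are considered. At stake are a few points of power and a somewhat wider interval at the same number of patients. Bias and false-positive control are not in question.

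**Working it through.** **Inputs.** From Sample size: 76% v 53%, α 0.05, power 90%, 20% dropout. The figure 88 is read as per group because 88/0.80 = 110. Sample size does not state sidedness. Statistical analysis says "to control the one-error rate at 5% (two-sided" when describing the sequential secondary tests, and two-sided is used here. The correlation rho between a baseline score and ACR20 response is **not in the documents** and is varied from 0.1 to 0.5.

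**1. The plan's own figure.** With mean rate 0.645 and pooled variance under the null:

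n = [1.960·√(2·0.645·0.355) + 1.282·√(0.76·0.24 + 0.53·0.47)]² / 0.23² = 4.701/0.0529 = 88.9, or 89 per group.

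The stated 88 agrees to within rounding (the arcsine formula gives 88.7). One-sided testing would give 73, so 88 implies a two-sided test. It is a normal-approximation figure, not one for Fisher's test.

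**2. Cost of Fisher's test, with no covariates (exact enumeration).** If the 20% dropouts would have responded at the planning rates, counting them as failures gives 0.8·76% = 60.8% and 0.8·53% = 42.4%.

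| Setting | Fisher | Chi-square | Difference |
|---|---|---|---|
| 88 per arm, 76% v 53% | 86.7% | 89.9% | 3.2 |
| 110 per arm, 60.8% v 42.4% | 74.3% | 78.5% | 4.2 |

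At 88 per arm and a common rate of 64.5%, Fisher's actual type I error is about 3.4%. It needs about 98 per arm for 90% power.

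**3. Covariate gain at 88 per arm.** Power ≈ Φ(d/SE − 1.96), where the unadjusted SE = √(0.76·0.24/88 + 0.53·0.47/88) = 0.0700 and adjustment multiplies it by √(1 − rho²). Here d = 0.23.

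| rho | SE | Power | Gain |
|---|---|---|---|
| 0 | 0.0700 | 90.7% | – |
| 0.1 | 0.0697 | 91.0% | +0.3 |
| 0.2 | 0.0686 | 91.8% | +1.1 |
| 0.3 | 0.0668 | 93.1% | +2.4 |
| 0.5 | 0.0606 | 96.7% | +6 |

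The 90.7% starting point is this formula's unadjusted value (unpooled SE). It should not be mixed with the exact 89.9% in step 2.

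**4. Covariate gain at 110 per arm with imputation.** If dropout is unrelated to baseline, recoding 20% of patients as failures dilutes rho by 0.8·√(0.645·0.355/(0.516·0.484)) = 0.8·√(0.229/0.250) = 0.77. The unadjusted SE is 0.0662 and d = 0.184, giving 79.3%.

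| rho before imputation | rho after | Power | Gain |
|---|---|---|---|
| 0.3 | 0.23 | 81.4% | +2.1 |
| 0.5 | 0.38 | 85.3% | +5.9 |

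**5. Check by simulation.** A logistic model with one baseline covariate, standardised to a risk difference, was run 4,000 times per setting. At 88 per arm it gave power of 90.0%, 91.8% and 93.4% for R² of about 0.02, 0.07 and 0.13. Chi-square on the same data gave 89.4%, 90.0% and 89.7%, so the gains were about 0.7, 1.8 and 3.7 points. Type I error of the adjusted test, simulated at 110 per arm with both rates at 60%, was 5.2% to 5.3%.

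**6. Centre alone.** In simulation with ten centres, adjusting for centre added 0.4 to 1.0 points when centre effects had SD 0.5 on the logit scale, and 2 to 3 points at SD 1.0. Both SDs are assumptions.

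**The case against.** The strongest reply is that nothing here is an error. Fisher's test is valid under randomisation, an unadjusted primary test is a common choice, and covariate lists usually belong in an analysis plan that is not shown. The first two statements stand, and they limit the point to efficiency. The third does not remove it, because this article names the test, and an adjusted primary model written later would depart from it.

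The second objection concerns size, and most of it stands. ACR20 is already defined by change from baseline, so baseline components may predict it only weakly. At rho 0.1 to 0.2 the gain is about a point or less.

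A reader might infer more than the documents support, in three ways:

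- **A gain of about 10 points once dropouts count as failures.** Leaving rho at 0.5 after imputation does give 79.3% to 89.4%. That requires 0.5 to be the correlation after recoding; with dropout unrelated to baseline the gain is about 6.
- **That non-responder imputation by itself brings the gain to 5 points.** At rho 0.3 the gain is +2.1 with dilution and only +3.6 even without it. Strong prediction is needed.
- **That ten centres and 1:1 allocation oblige the analysis to adjust for centre.** The sentence on sites is ambiguous and no stratification or blocking by centre is stated. Centre is therefore a precision option, and at moderate variation a small one.

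**Conclusion.** The point holds as a loss of efficiency. The plan fixes a primary test that cannot use baseline data the trial already collects.

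Two separate amounts are involved. Moving off Fisher's test is worth 3 to 4 points of power and needs no covariate. Adjustment adds a further amount that depends on an unknown correlation: from almost nothing, through about 2 points at rho 0.3, to about 6 at an optimistic 0.5. This holds both at 88 per arm and at 110 with imputation.

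These figures assume the planning rates, two-sided 5% testing and a variance reduction of 1 − rho². The imputed case also assumes equal 20% dropout in both arms, unrelated to baseline, among patients who would otherwise have responded at the planning rates.

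**What to change.** In Statistical analysis (stage two), state that the primary week-24 ACR20 comparison is a covariate-adjusted marginal risk difference with its 95% CI, obtained from a logistic model by standardisation. Name two or three Visit 2 covariates in advance, for example joint counts, HAQ, and CRP or ESR. Include centre, with small centres pooled, if allocation is in fact balanced by site; otherwise treat it as an optional precision term. At about 22 patients per centre (220/10), the pooling rule should be written down. Keep Fisher's exact test as a sensitivity analysis.

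The cost is wording: no new data and no more patients. The covariates and a rule for missing baseline values must be fixed before unblinding.

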### Withdrawal criteria

Patients would be withdrawn from the study if the clinician found that they were in need of or were better served with another treatment or if the exclusion criteria were met. Patients would also be withdrawn from the study if according to the clinician's judgment clinical conditions worsened or if the patients withdrew their consent. The date and reason for discontinuation were noted. All patients who prematurely discontinue the trial would undergo a final evaluation.

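### Observed cases are the primary analysis of the continuous secondary endpoints despite the intent-to-treat promise, and the use of withdrawal-visit values is undefined

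*Protocol article*

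**What the plan says.** The stage-two Statistical analysis section sets the population: "All efficacy endpoints will be analyzed using the intent-to-treat analysis set, which will include all randomized patients regardless of whether they received an investigational product". It then splits the handling of missing data by type of variable. For yes/no endpoints, "For dichotomous variables, missing values will be imputed using a non-responder imputation method"; for the rest, "for continuous variables, the primary analysis will be based on observed cases". All secondary endpoints are to be tested in a pre-specified order at 5% two-sided.

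The stage-two Outcome measures section makes the individual ACR components secondary endpoints alongside ACR50 and ACR70. Table 2 shows how such components are measured: joint counts, global assessments, pain, HAQ, CRP and ESR. These are scores, counts and laboratory values, so the observed-case rule governs most of them.

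Withdrawal rules appear only in the stage-one part, under Withdrawal criteria. Patients leave "if the clinician found that they were in need of or were better served with another treatment", and further: "Patients would also be withdrawn from the study if according to the clinician's judgment clinical conditions worsened". The same section adds: "All patients who prematurely discontinue the trial would undergo a final evaluation". Stage two has no withdrawal section of its own, but its Sample size section allows for 20% dropout. Table 2 heads Visit 9 "24^th ^w (or withdrew", that is, week 24 or the withdrawal visit.

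**The concern.** An observed-case analysis cannot include a patient who has no value, so for continuous endpoints the intent-to-treat promise is met only for those who were measured. The two missing-data rules also pull apart. A patient withdrawn for worsening, with no later value, counts against the arm on ACR50 but disappears from that arm's joint counts and HAQ.

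If withdrawal is more frequent in one arm, or more closely tied to poor outcome there, that arm loses more of its worst results and looks better than it should. The arms are different drug combinations, so unequal withdrawal is plausible. At stake is the 5% error control claimed for the sequentially tested secondary endpoints. The primary endpoint is not at stake.

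**Working it through.** **The plan's own figures.** Inputs from the Sample size section: 76% v 53% ACR20, α = 0.05 (taken as two-sided), β = 0.10, 20% dropout.

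- n per arm = [1.960·√(2·0.645·0.355) + 1.282·√(0.76·0.24 + 0.53·0.47)]² / 0.23² = 88.9, against the stated 88.
- 88 / 0.8 = 110 per arm, 220 in all.
- 20% of 220 = 44 patients. If none of them has a usable value, the continuous comparisons rest on 176.

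**What happens to a withdrawn patient.** The text allows three outcomes:

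1. The withdrawal assessment does not count as week 24. The patient is left out.
2. It counts as week 24. The patient stays in, but a value from, say, week 4 is compared with values from week 24.
3. The patient is lost without a final assessment. The patient is left out whichever rule applies.

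**Size if values are left out.** The documents give no SD for continuous endpoints, no dropout by arm and no link between dropout and outcome. Assumptions: SD 1, no true difference, 110 per arm, two-sample test at 5%. Patients drop out when a latent score, correlated r with outcome, falls in its lowest fraction d.

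- Let c be the d-quantile of the standard normal and m(d) = φ(c)/(1 − d).
- The mean of retained patients is shifted by r·m(d). Their variance is 1 − r²·m·(m − c).
- m(0.10) = 0.195; m(0.15) = 0.274; m(0.20) = 0.350; m(0.25) = 0.424; m(0.30) = 0.497.
- Bias = r·[m(d₂) − m(d₁)], in favour of the arm with more dropout.
- Error rate = Φ(−1.96 + bias/SE) + Φ(−1.96 − bias/SE).

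| Dropout | r | Bias (SD) | SE | Error rate |
|---|---|---|---|---|
| 20% v 20% | 0.6 | 0 | 0.139 | 5% |
| 15% v 25% | 0.3 | 0.3 × 0.149 = 0.04 | 0.148 | 6% |
| 15% v 25% | 0.6 | 0.6 × 0.149 = 0.09 | 0.139 | 10% |
| 10% v 30% | 0.6 | 0.6 × 0.302 = 0.18 | 0.140 | 25% |

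Simulation of 20,000 trials per row agrees to within 1 percentage point. Every split averages the planned 20%. The rates are for one stand-alone test, not for the whole testing sequence.

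**Whether the remedy helps.** I simulated dropout driven by an earlier visit correlated 0.6 with week 24, at 10% v 30%. The observed-case bias was 0.18 SD. Using the earlier visit in the estimate, as a likelihood-based model does, reduced it to about 0.

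**The case against.** The strongest reply is that withdrawn patients are due an assessment. The stage-one text requires a final evaluation, and Table 2 schedules joint counts, global assessments, VAS, HAQ, CRP and ESR at Visit 9, whether that falls at week 24 or at withdrawal. A reader might infer that the week-24 comparisons are made only among patients who did well. The documents do not support that, because the worst patients may well have an observed last value. What stands is that the article does not say how that value is used, and both readings leave a problem.

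Second, the rule on withdrawing patients who worsen belongs to stage one. Carrying it into stage two is a reasonable inference, since stage two expects withdrawals and gives no other criteria, but it is not stated.

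Third, a reader might infer that type I error is certainly not controlled. That does not follow either. The plan assumes a single 20% dropout rate, and with equal dropout equally tied to outcome the bias is 0 under no true difference. Error control is not assured, which is a weaker statement.

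Fourth, an intent-to-treat set fixes who is eligible and in which arm, while observed cases means only that nothing is imputed. Formally the two can coexist, and an article may leave the model to the analysis plan. But the article has fixed observed cases as the primary analysis. A later plan that retained all randomised patients would have to depart from it, so this is a stated choice and not an omitted detail.

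**Conclusion.** The point holds in a limited form. The primary analysis of the continuous endpoints leaves out randomised patients without a value, contrary to the aim stated in the same paragraph, and the status of withdrawal-visit values is undefined. The possible bias ranges from none, when withdrawal is alike in the two arms, to about 0.18 SD with a 25% single-test error rate at 10% v 30% dropout and a correlation of 0.6. A more moderate 15% v 25% split gives 0.04 to 0.09 SD and 6% to 10%. All these figures rest on assumed splits and correlations, on withdrawn patients having no usable value, and on stage-one withdrawal practice applying in stage two. ACR20, ACR50 and ACR70 are protected from this problem by non-responder imputation. The change should be made, but the trial's main conclusion does not depend on it.

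**What to change.** Amend the stage-two Statistical analysis section as follows.

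- **Primary analysis of continuous endpoints:** a baseline-adjusted mixed model for repeated measures on all randomised patients, using the visits in Table 2. These are weeks 2, 4, 8, 12, 16, 20 and 24 for joint counts and global assessments; the same from week 4 for VAS; and weeks 12 and 24 for HAQ, CRP and ESR.
- **Withdrawal assessments:** enter each at its actual week and do not relabel it as week 24.
- **Sensitivity:** one missing-not-at-random analysis, for example delta-adjusted or reference-based multiple imputation. It matters most for HAQ, CRP and ESR, where only one scheduled post-baseline visit precedes week 24 and the model has little to borrow from.
- **Observed cases:** keep as supportive.
- **Withdrawal criteria:** state whether the stage-one criteria and the final evaluation apply in stage two.

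The cost is wording and a little more programming, with no new data or patients. The model relies on a missing-at-random assumption and will not remove bias from dropout that depends on outcomes never recorded. The sensitivity analysis is there to test that assumption.
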